### Sample size and statistical methods

Considerations for the sample size calculations are based upon data from the Uppsala-Gävle pilot study,
[15] together with data from the National Registry of Cardiac Arrest in Sweden
[19]. It was assumed that in the conventional manual treatment group, the proportion of four-hour survival will be 25% and in the LUCAS-CPR treatment group the proportion of four hour survival will be at least 31%. To detect the anticipated difference of at least 6% with a power of 90% in the final analysis, the study requires a total of 2500 patients, i.e. 1250 patients in each treatment group in the intention to treat population. For the intention to treat and predefined populations the primary and all secondary endpoints will be compared between treatment groups with frequency tables and two-sided Fisher’s Exact Tests at the 4.8% and 5% level, respectively; 95% confidence intervals for difference in proportions will be presented where applicable. The result for the primary endpoint in the intention to treat population is confirmative while the other results are regarded as supportive.

Injuries after CPR will be studied in detail. The proportions of patients will be compared between the two treatment groups with frequency tables and two-sided Fisher’s Exact Test at 5% level.

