### Analysis populations

The analysis populations are defined as:

Safety population: all randomised patients except surviving patients without informed consent. Intention to treat (ITT) population: all randomised patients except surviving patients without informed consent. Predefined population (PP): all randomised patients, except surviving patients without informed consent, who have completed the study treatment without any protocol violations. Possible protocol violations are:

• Inclusion criterion not fulfilled.

• Primary exclusion criteria subsequently confirmed to have been present.

• Dispatch time to ambulance stop at the address exceeding 12 min.

• Cardiac arrest not witnessed by sight or sound (If data are missing regarding whether the cardiac arrest was witnessed or not, the patient should be regarded as not witnessed).

• LUCAS™ Chest Compression System not brought to the patient or no record form filled in.

If the actual treatment given is not that to which the patient was randomised, the patient will be included in the ITT population set as randomised, but in the PP population according to the actual treatment.

For missing data, the primary endpoint and the first four of the secondary endpoints will be defined according to the worst case principle, i.e. as failures in the ITT population. The confirmative analysis will be performed in the ITT population. The PP analysis will be regarded as supportive. In the PP analysis no imputation of missing values will be performed.

An interim analysis of the primary endpoint was performed during spring 2011 by an independent safety committee within the Scandinavian Society of Anaesthesiology and Intensive Care Medicine research group (SSAI). This was done according to protocol, after 1500 patients had been randomized, using the primary endpoint i.e. 4 h of ROSC, and performed on the intention to treat population. In the interim analysis the criterion for terminating the study is that the p-value from a two-sided Fisher’s Exact Test is less than 0.005. A group-sequential analysis plan
[20] is used to preserve a Type I error of at most 5%, so that after completion of the study the primary hypothesis will be tested at a level of 4.8%.

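### The primary endpoint is tested at 4.8% but the only stated confidence level is 95%, so the interval can exclude zero when the confirmatory test fails

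*Protocol article*

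**What the plan says.** Under Sample size and statistical methods, the article plans "two-sided Fisher’s Exact Tests at the 4.8% and 5% level, respectively". The word 'respectively' could pair the two levels with the two populations or with primary and secondary endpoints. On either reading the primary endpoint in the intention-to-treat population is tested at 4.8%. The same sentence goes on: "95% confidence intervals for difference in proportions will be presented where applicable". No other confidence level appears. The next sentence sets the hierarchy: "The result for the primary endpoint in the intention to treat population is confirmative while the other results are regarded as supportive".

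Under Analysis populations, the article explains the reduced level. The interim analysis took place "after 1500 patients had been randomized", and the stopping criterion was that "the p-value from a two-sided Fisher’s Exact Test is less than 0.005". The group-sequential plan "is used to preserve a Type I error of at most 5" per cent, and at the end of the study "the primary hypothesis will be tested at a level of 4.8" per cent.

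**The concern.** Two test levels are fixed but only one interval level, and it does not match the confirmatory test. A reader who checks whether a 95% interval excludes zero is applying a 5% test, which the group-sequential plan had rejected for this comparison.

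In a borderline result, the report could show an interval that excludes no difference next to a primary test that is not significant. In all tables examined the conflict ran in this one direction, so the interval would always be the more favourable of the two statements. What is at stake is how a borderline result is read.

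**Working it through.** **Inputs from the article.** Interim after 1500 of 2500 patients, so the information fraction is 1500/2500 = 0.60. Interim boundary p < 0.005, final level 0.048, both two-sided Fisher. Design rates 25% and 31%, with 1250 per arm.

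**Assumption.** The article names no interval method. Two are used here to give a range: the Wald interval, d ± z·SE with SE = √(p₁q₁/n + p₂q₂/n), and the same interval with a continuity correction, which adds ½(1/n + 1/n) = 1/1250 = 0.08 points on each side.

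**1. The plan's own level.** Overall alpha = 1 − P(|Z₁| < c₁ and |Z₂| < c₂), with correlation √0.60 = 0.775 and c₁ = 2.807 (for 0.005).
- Final level 0.048, c₂ = 1.977: overall alpha 0.0493. The 4.8% figure is confirmed.
- Final level 0.05, c₂ = 1.960: overall alpha 0.0513, above the 5% ceiling.

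The stated size also fits: exact enumeration of Fisher's test at 0.048 with 1250 per arm gives 90.7% power for 25% vs 31%, against the planned 90%.

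**2. An example of the conflict.** 344/1250 vs 300/1250: 27.52% vs 24.00%, d = 3.52 points, SE = 1.748 points, Fisher p = 0.0492. This would pass at 5% and fails at 4.8%.
- 95% Wald: 3.52 ± 1.960 × 1.748 = +0.09 to +6.95.
- 95% with continuity correction: +0.01 to +7.03, which still excludes zero.
- 95.2% Wald: 3.52 ± 1.977 × 1.748 = +0.06 to +6.98, which still excludes zero.
- 95.2% with continuity correction: −0.02 to +7.06, which agrees with the test.

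**3. How often.** The 2×2 tables at 1250 per arm were enumerated with binomial weights. The last four rows give the chance that the interval excludes zero while Fisher p ≥ 0.048.

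| | 25% vs 25% | 28% vs 25% | 31% vs 25% |
|---|---|---|---|
| Level alone: 0.048 ≤ Fisher p < 0.05 | 0.18% | 0.66% | 0.29% |
| 95%, continuity-corrected | 0.20% | 0.74% | 0.32% |
| 95%, Wald | 0.71% | 2.44% | 1.01% |
| 95.2%, Wald | 0.51% | 1.77% | 0.73% |
| 95.2%, continuity-corrected | 0.02% | 0.07% | 0.03% |

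The reverse conflict (test rejects, 95% interval includes zero) had probability 0 in each scenario.

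Moving a Wald interval to 95.2% removes only about 28% of its conflicts (for example, (0.71 − 0.51)/0.71). The remainder comes from pairing a non-exact interval with Fisher's test. Level and method must both be matched.

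**4. Cost in width.** At 31% vs 25%, SE = √(0.31 × 0.69/1250 + 0.25 × 0.75/1250) = 1.792 points. The half-width goes from 1.960 × 1.792 = 3.51 to 1.977 × 1.792 = 3.54 points, a ratio of 1.009.

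**The case against.** The strongest reply is that the article already says what governs. The primary intention-to-treat test is the confirmatory result, and the interval is only presented, where applicable, and is correctly labelled 95%. Nominal 95% intervals next to an alpha-adjusted test are a common convention. This stands as far as error control goes. A reader might infer that the type I error is inflated; it is not, because the decision rests on the Fisher test at 4.8%. The reply does not remove the mismatch, since a difference in proportions plainly applies to the primary endpoint and no other level is offered for it.

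A second reply is that the interval method is unnamed and may be fixed in a document not shown. That also stands, and it limits the size of the point. A reader might take the Wald frequencies (0.7%, 2.4%, 1.0%) as the size of the level mismatch, or cite a result such as 356 vs 312 of 1250. That result has Fisher p = 0.0519, so it fails at 5% as well. Its 95.2% Wald interval, +0.02 to +7.02 points, still excludes zero, so the conflict there comes from the assumed method and not from the level.

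A reader might also infer that manufacturer sponsorship makes a misleading claim likely. The article does not support this: an academic research centre holds the database and performs the analyses, and the manufacturer's steering committee members are non-voting.

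**Conclusion.** The point holds as a minor inconsistency in the stated text. The 95% interval matches a 5% final test, which would take overall alpha to about 0.0513, while the plan tests at 4.8% (0.0493).

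The effect of the level alone is small: about 0.2% of trials with no effect, 0.7% at 28% vs 25%, and 0.3% at 31% vs 25%. With the interval method included, the ranges are about 0.2–0.7%, 0.7–2.4% and 0.3–1.0%, from continuity-corrected to Wald. These figures assume exactly 1250 per arm and one of those two methods. The alpha figures use the normal approximation for two looks. Neither the test nor the sample size needs to change.

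**What to change.** State, before the final analysis, that for the primary endpoint in the intention-to-treat population a 95.2% confidence interval for the difference in proportions will be given, by a named method consistent with the planned unstratified Fisher test, and that the test governs the conclusion. Of the two methods tried here, the continuity-corrected interval comes close to full agreement. The sentence on precedence is still needed, because inverting Fisher's conditional test gives an interval for the odds ratio and not for the difference. A site-stratified score or Cochran–Mantel–Haenszel interval would not do: it does not invert an unstratified test and would bring in a new mismatch.

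Keep 95% intervals for the other endpoints and label them unadjusted.

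The cost is one or two sentences and an interval about 1% wider (half-width 3.51 to 3.54 points at the design rates). If a continuity correction is chosen, it adds a further 0.08 points on each side.

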### Analysis populations

The analysis populations are defined as:

Safety population: all randomised patients except surviving patients without informed consent. Intention to treat (ITT) population: all randomised patients except surviving patients without informed consent. Predefined population (PP): all randomised patients, except surviving patients without informed consent, who have completed the study treatment without any protocol violations. Possible protocol violations are:

• Inclusion criterion not fulfilled.

• Primary exclusion criteria subsequently confirmed to have been present.

• Dispatch time to ambulance stop at the address exceeding 12 min.

• Cardiac arrest not witnessed by sight or sound (If data are missing regarding whether the cardiac arrest was witnessed or not, the patient should be regarded as not witnessed).

• LUCAS™ Chest Compression System not brought to the patient or no record form filled in.

If the actual treatment given is not that to which the patient was randomised, the patient will be included in the ITT population set as randomised, but in the PP population according to the actual treatment.

For missing data, the primary endpoint and the first four of the secondary endpoints will be defined according to the worst case principle, i.e. as failures in the ITT population. The confirmative analysis will be performed in the ITT population. The PP analysis will be regarded as supportive. In the PP analysis no imputation of missing values will be performed.

An interim analysis of the primary endpoint was performed during spring 2011 by an independent safety committee within the Scandinavian Society of Anaesthesiology and Intensive Care Medicine research group (SSAI). This was done according to protocol, after 1500 patients had been randomized, using the primary endpoint i.e. 4 h of ROSC, and performed on the intention to treat population. In the interim analysis the criterion for terminating the study is that the p-value from a two-sided Fisher’s Exact Test is less than 0.005. A group-sequential analysis plan
[20] is used to preserve a Type I error of at most 5%, so that after completion of the study the primary hypothesis will be tested at a level of 4.8%.

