### Patient consent

The nature of the study, in relation to patients who are unconscious, precludes consent before enrolment. It is the responsibility of the investigator to provide, for each surviving subject with mental capacity, full and adequate verbal and written information about the objectives and procedures of the study. They are given the opportunity to ask questions and to decide whether or not they are willing for their results to be included in the dataset. They are also told of their freedom to withdraw from the study at any time and that withdrawal will not affect their future medical care. In cases where the subjects survive without having the mental capacity to accept or withdraw participation, written information is presented to the family, who then take the decision to continue participation or not. Subjects included who do not survive will stay in the study; the family will not be asked for consent. This prevents any positive bias in the results.

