### Efficacy and safety evaluation in the study

For efficacy evaluation the following primary and secondary endpoints that will be analysed in the study are:

1. Primary endpoint

a. Four-hour survival after successful restoration of spontaneous circulation (ROSC).

2. Secondary endpoints

a. Restoration of spontaneous circulation defined as a spontaneous palpable pulse.

b. Arrival to the emergency room with spontaneous palpable pulse.

c. Survival to discharge from ICU without severe neurological impairment (CPC 1 or 2).

d. Survival to hospital discharge without severe neurological impairment (CPC 1 or 2).

e. Survival 1 and 6 months after cardiac arrest without severe neurological impairment (CPC 1 or 2).

The safety evaluation in the study comprises three main areas. The first relates to serious adverse events or serious adverse device events. These cover events directly related to CPR, as judged by investigator/co-investigator, and assumed to occur after the randomisation in the study with any of the following sequelae: death; serious deterioration of health in patient; life threatening illness or injury, permanent deterioration of body function or structure; prolongation of hospitalisation; conditions that require medical or surgical treatment to prevent any of the foregoing.

The second area for safety evaluation is any post mortem examination that may reflect injuries from CPR. For comparison of injuries from the two different CPR techniques, autopsies are performed to quantify the number of injuries possibly affecting survival. They are undertaken in three centres (Uppsala, Gävle, and Västerås in Sweden). The aim is to obtain autopsy results from a total of 300 study patients with 150 who have received manual chest compressions only and 150 after LUCAS™ chest compressions.

The third area relates to the criteria for termination of the study stated in the protocol (described above) that would be considered by the steering committee, sponsor, and the independent safety committee within the Scandinavian Society of Anaesthesiology and Intensive Care Medicine research group (SSAI).

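### The set called intention to treat drops only survivors who do not consent, so the confirmatory four-hour survival test is conditioned on a near-proxy of its own outcome

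*Protocol article*

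**What the plan says.** The section Analysis populations gives this definition: "Intention to treat (ITT) population: all randomised patients except surviving patients without informed consent". The safety set has the same definition, and the predefined population applies the same exclusion before its own criteria. The section then states: "The confirmative analysis will be performed in the ITT population". The interim analysis was also run on this set.

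The section Patient consent explains how removal comes about. Consent before enrolment is impossible. Survivors with mental capacity are informed afterwards and decide whether their results may be used; for survivors without capacity the family decides. For the dead the rule is: "Subjects included who do not survive will stay in the study; the family will not be asked for consent". The section adds: "This prevents any positive bias in the results".

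The primary endpoint is survival to four hours after return of spontaneous circulation. The sample size section assumes 25% with manual CPR and 31% with LUCAS, and asks for "1250 patients in each treatment group in the intention to treat population". The final test is a two-sided Fisher's exact test at 4.8%. Missing primary outcomes count as failures, but only within the ITT set.

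**The concern.** Membership of the confirmatory set depends on something that happens after randomisation and is closely tied to the endpoint. A patient who dies before consent is sought can never leave the set. A patient who leaves it was alive when asked, and so in practice had already survived four hours. Successes can be deleted and failures cannot.

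Two things follow. The survival proportion is pushed down in each arm. And the comparison stays fair only if the chance of removal among survivors is the same in both arms, which randomisation does not secure. Consent comes after treatment and outcome, patients and families are told about the study, and no masking of them is described.

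Nothing else in the article repairs this. The rule that missing means failure does not reach patients outside the set, and no described analysis keeps every randomised patient. The trial's only confirmatory result rests on this set.

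**Working it through.** **Inputs.** From the sample size and analysis population sections: 25% vs 31%, 1250 per arm, two-sided 4.8%, planned power 90%. Not in the article, so assumed: r, the share of four-hour survivors removed for lack of consent, taken between 2% and 10%. 'Surviving' is given no time point; I assume that a removed patient had already survived four hours. I treat 1250 per arm as the number before removal.

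**Plan's own figure.** The two-proportion formula with continuity correction at 4.8% and 90% power gives 1221 per arm, 2442 in total, within 3% of 2500. At 1250 per arm, power is 91.4% by normal approximation and about 90.8% by simulated Fisher's exact test. The sample size is not in dispute.

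**Effect of removal.** With true survival p, the observed proportion is

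p(1 − r) / (1 − p·r).

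The observed odds are p(1 − r)/(1 − p), so the odds ratio is multiplied by (1 − r_LUCAS)/(1 − r_manual). Equal refusal leaves the odds ratio, and hence the null, unchanged.

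**Equal refusal, true 25% vs 31%**

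- r = 2%: 24.6% vs 30.6%, difference 5.9 points, power 91.0%.
- r = 5%: 0.25 × 0.95 / (1 − 0.0125) = 24.1%, and 0.31 × 0.95 / (1 − 0.0155) = 29.9%. Difference 5.9 points, power 90.4%.
- r = 10%: 23.1% vs 28.8%, difference 5.7 points, power 89.3%.

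**Unequal refusal, true 25% vs 31%**

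- Manual 2%, LUCAS 5%: difference 5.3 points, power 83.6%.
- Manual 5%, LUCAS 2%: difference 6.5 points, power 95.2%.
- Manual 2%, LUCAS 8%: difference 4.6 points, power 73%.
- Manual 8%, LUCAS 2%: difference 7.1 points.

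**No true effect, 25% in both arms.** Rejection probability of the final test at 4.8%, by pooled normal approximation:

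- Equal refusal: 4.8%.
- 2% vs 5%: 24.6% vs 24.1%, spurious difference 0.6 points, type I error about 6.0%.
- 2% vs 8%: 24.6% vs 23.5%, spurious difference 1.15 points, type I error about 10%. This comes from 1250 × 0.25 × 0.02 ≈ 6 removals in one arm and 1250 × 0.25 × 0.08 = 25 in the other.
- 2% vs 8% among those asked, if only 40% of four-hour survivors live to be asked: effective shares 0.4 × 2% = 0.8% and 0.4 × 8% = 3.2%, spurious difference 0.45 points, type I error about 5.6%. The 40% is also an assumption.

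**The case against.** The strongest reply is that material harm needs refusal to differ by arm, and nothing in the article shows that it did or would. Survivors and families are told the aims and procedures of the study; the article does not say that they are told the allocated arm. With equal refusal the test keeps its level, and even 10% in both arms costs only about 2 points of power (91.4% to 89.3%). Patients who die before being asked stay in, which dilutes the effect further. All of this stands.

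A reader might therefore infer too much from the definition: that the type I error is in fact no longer 4.8%, or that the trial lost a large part of its power. The article does not support either. The 10% and 73% figures need a fourfold imbalance in refusal and every four-hour survivor being asked, and both are assumptions.

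A reader might also conclude that the sentence "This prevents any positive bias in the results" is false. It is not. It concerns keeping the dead without asking their families, and that does prevent an upward bias. It is incomplete, because it does not mention the downward bias from removing survivors.

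Finally, survivors may decline to have their results used, so the ethics approvals may bar putting refusers back into the main analysis. That limits the remedy. It does not make the set intention to treat, because the definition is part of the article's own text and not a detail left to an analysis plan.

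**Conclusion.** The point holds in a limited form and should be fixed; it does not invalidate the design. The confirmatory set is selected after randomisation on a near-proxy of four-hour survival and is wrongly labelled intention to treat. Survival is understated in both arms. Under equal refusal the null and the 4.8% level are intact and the effect is slightly attenuated. Under unequal refusal the difference can move either way and the level is not guaranteed: from about 5.6% to about 10% in the scenarios above. These figures rest on assumed refusal rates, on removed patients having survived four hours, and on a normal approximation for the final test alone. The true size and direction cannot be known from the article.

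The supportive endpoints that require CPC 1 or 2 have the same gap, but a removed survivor may be a success or a failure on them, so the direction of any bias there is open. That families refuse selectively for severely impaired survivors is something a reader might suppose, but the article gives no evidence for it.

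**What to change.** - Call the present set 'modified ITT' wherever it is used, including the interim analysis.
- Report the number of non-consenting survivors removed, by arm.
- Pre-specify, before the comparative results are seen, a key sensitivity analysis of all randomised patients. It adds these survivors to numerator and denominator as four-hour survivors, as an anonymous count per arm where the ethics approvals allow. Where they do not, give bounds. Make this the primary analysis only if the approvals expressly permit it.
- For the CPC endpoints, give best-case and worst-case bounds, with the removed survivors counted as all CPC 1 or 2 and as none.
- In Patient consent, add that removing non-consenting survivors can bias survival downwards.

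The cost is a little extra analysis and a confirmation from the ethics boards that an arm-level count may be used. Arm and four-hour status of each refuser must be known to form that count, which is why the confirmation is needed. No new patients and no change of sample size are required, and the analysis can be added although enrolment has ended.

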### Study enrolment and randomisation

The device is brought to all patients with dispatch codes for sudden cardiac arrest, loss of consciousness, or other local guidelines suggesting OHCA. Enrolment into the study is at the time that paramedics recognise the situation as a cardiac arrest after they arrive on scene. After confirmation of the arrest, one ambulance professional immediately starts manual CPR while another takes care of the randomisation procedure. All patients fulfilling the inclusion criteria and having no known exclusion criteria are randomised using block randomisation with site (EMS) as stratification variable. Block size is set to 6, but has been kept unknown to all personnel involved throughout the study. Randomisation is at the patient’s side by opening an envelope which is enclosed in the LUCAS™ back pack. Inside the envelope there will be a note prompting either conventional manual or LUCAS™ CPR. A replacement envelope from the block of 6 is added to the LUCAS pack after each use.

Patients suffering a cardiac arrest witnessed by the ambulance crew are handled according to a separate algorithm and if eligible they are randomized into the study (Figure
1).

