### The LUCAS™ algorithm

Patients randomised to LUCAS™ CPR are treated initially with manual compressions with minimised interruptions until the device is unpacked and ready to use. LUCAS™ is attached to the patient as soon as possible. In this group the defibrillator must be in manual mode. Mechanical compressions are continued initially for 3 min without checking heart rhythm, irrespective of any manual compressions that have been given by bystanders. The sequence is not interrupted for a shock that is delivered during compressions after 90 seconds of this first 3 min cycle, with the remaining 90 seconds of continued compressions to follow. Thus, the first shock is given on the basis only of definite cardiac arrest without knowledge of whether it is or is not ‘shockable’. Subsequently, heart rhythm is determined after each 3 min cycle by interrupting mechanical compressions briefly and never for longer than 10 seconds. If the analysed rhythm is shockable, a new 3 min cycle of compressions is started, incorporating as before one shock delivered after 90 seconds of on-going compressions. If the rhythm is not shockable, a 3 min cycle of compressions without any shock is followed by a new rhythm analysis. Heart rhythm and circulation are checked after each 3 min cycle (Figure
2).

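### The supportive PP comparison groups patients by treatment received, so early outcome can decide the arm; the direction and size of the resulting bias cannot be derived from the article

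*Protocol article*

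**What the plan says.** The protocol article, Analysis populations, restricts PP (there called the predefined population) to patients "who have completed the study treatment without any protocol violations". It then gives a rule for patients whose treatment differed from their allocation: "the patient will be included in the ITT population set as randomised", "but in the PP population according to the actual treatment". Receiving the other arm's treatment is not on the list of possible violations.

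Sample size and statistical methods compares the treatment groups in both populations with a two-sided Fisher's exact test, at 4.8% and 5% respectively. No adjustment for regrouping is described. The ITT result for the primary endpoint is confirmative; for the other set, "The PP analysis will be regarded as supportive".

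Two other sections bear on who receives the device. At the scene, "one ambulance professional immediately starts manual CPR while another takes care of the randomisation procedure" (Study enrolment and randomisation). Patients allocated to LUCAS "are treated initially with manual compressions with minimised interruptions until the device is unpacked and ready to use" (The LUCAS algorithm).

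**The concern.** An analysis by treatment received sets group membership after randomisation. That is safe only if receipt of the device is unrelated to prognosis, and here there is a direct route by which it may not be. Every LUCAS-arm patient goes through a manual phase first, and what happens in that phase can determine whether the device is attached at all. Regaining a pulse is the first step towards the primary endpoint, so the outcome itself can help to decide the arm.

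At stake is what the PP result can be used for. It is meant to support the confirmative result, but part of any gap between the two could come from regrouping. A secondary problem is wording: a patient who received the other arm's treatment has not obviously completed the study treatment, yet the crossover clause keeps that patient in PP and switches the arm.

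**Working it through.** **1. The plan's own figure.** Inputs from Sample size and statistical methods: 25% versus 31%, 90% power, two-sided 4.8%, 1250 per arm. With z(0.976) = 1.977 and z(0.90) = 1.282, the normal approximation n = [1.977·√(2·0.28·0.72) + 1.282·√(0.25·0.75 + 0.31·0.69)]² / 0.06² gives 1188 per arm. The continuity correction that approximates Fisher's test raises this to 1221, or 2442 in total, against 2500 stated. Power at 1250 per arm is 91.4%. The plan's figure is reproduced, and the PP rule does not affect it.

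**2. Who can change arm in PP.**
- LUCAS arm, ROSC before attachment: survival probably above the arm average. If counted as manual, this biases against LUCAS.
- LUCAS arm, dead or stopped before attachment: no survivors. If counted as manual, this biases in favour of LUCAS.
- Manual arm, crossed to the device: still in arrest at that time, so probably a poorer prognosis. Counted as LUCAS, this tends to bias against LUCAS.

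**3. Regrouping arithmetic.** The article gives neither the share moved (f) nor its four-hour survival (s); both are assumed below. For movement from LUCAS to manual with equal arms:

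LUCAS rate = (pL − f·s)/(1 − f); manual rate = (pM + f·s)/(1 + f).

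Example with f = 5%, s = 80%, pL = 31%, pM = 25%, expected counts on 1250 per arm: 62.5 patients move, 50 of them survivors. LUCAS is (387.5 − 50)/1187.5 = 28.4%, manual is (312.5 + 50)/1312.5 = 27.6%, and the difference is 0.8 points.

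| Movement | Share | Assumed survival | Shown if true effect is 6 points | Shown if true effect is 0 (25% both) |
|---|---|---|---|---|
| LUCAS to manual | 1% | 60% | 5.4 | −0.7 |
| LUCAS to manual | 3% | 80% | 2.9 | −3.3 |
| LUCAS to manual | 5% | 50% | 3.8 | −2.5 |
| LUCAS to manual | 5% | 70% | 1.8 | −4.5 |
| LUCAS to manual | 5% | 80% | 0.8 | −5.5 |
| LUCAS to manual | 5% | 0% | 8.8 | +2.5 |
| Manual to LUCAS | 5% | 10% | 4.2 | −1.5 |

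Last row, for the 6-point case: (387.5 + 6.25)/1312.5 = 30.0% against (312.5 − 6.25)/1187.5 = 25.8%.

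**4. When the sign changes.** With no true effect, the movements out of the LUCAS arm cancel when the moved patients together survive at 25%. If there are k deaths before attachment for each early-ROSC patient, s/(1 + k) = 0.25, so k = s/0.25 − 1. That gives 1.4, 1.8 and 2.2 for s = 60%, 70% and 80%. Below k the net bias is against LUCAS; above it, in favour.

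**5. Base rate.** The 1250 per arm and the 25% and 31% are ITT figures. PP drops unwitnessed arrests and responses longer than 12 minutes, so its size and survival differ and are not given. If the PP base rate were 40% (assumed), 5% moved at 70% survival with no true effect gives (0.40 − 0.035)/0.95 − (0.40 + 0.035)/1.05 = 38.4% − 41.4% = −3.0 points, against −4.5 at a base rate of 25%.

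**The case against.** A reader might infer that the rule sends early-ROSC LUCAS patients to the manual group, biases PP against LUCAS and could cancel a true effect. The documents do not support that much, for four reasons.

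- The article does not define actual treatment for a patient with ROSC before attachment. Manual compression is the first step of the LUCAS algorithm, so such a patient can be read as having received the allocated treatment. A manual-only category does appear, in the autopsy target of "150 who have received manual chest compressions only and 150 after LUCAS™ chest compressions", but that describes the autopsy sample and not PP.
- The movements work in opposite directions. Deaths and cessations before attachment would favour LUCAS, and the mix is unknown.
- Cancelling a 6-point effect needs the extreme of the assumed range: 5% moved at 80% survival still leaves 0.8 points.
- ITT and PP can differ anyway because of the witnessed-arrest and 12-minute restrictions, so disagreement between them would be harder to read but not uninterpretable.

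The clash with the PP definition is also a tension in wording rather than a flat contradiction, because crossover is not a listed violation and has its own explicit clause.

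All of this stands, and it limits what can be said about direction and size. It does not rescue the rule. Grouping by treatment received is stated in the text, not left to another document, and a bias of unknown sign is no easier to use than one of known sign. PP already drops cases where the device was not brought to the patient or an exclusion criterion such as unsuitable body size was later confirmed. The non-receipt that remains is therefore more likely to follow the clinical course.

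**Conclusion.** The point holds as a weakness of the supportive analysis. The PP rule makes the comparison as-treated, and the manual phase in the LUCAS arm lets early outcome influence which arm a patient is counted in. Net direction and size cannot be derived from the article. The range of 5.4 to 0.8 points in place of 6, and of 8.8 when the moved patients all die, rests on assumed shares and survival, on ITT design figures, and on non-receipt of the device being read as manual treatment. The confirmative ITT test, its significance level, the interim rule and the sample size are untouched. The change should be made, but the trial's main conclusion does not depend on it.

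**What to change.** - Analyse the PP population by randomised arm.
- State that, for analysis, a LUCAS-arm patient with ROSC or cessation of resuscitation before attachment counts as treated per the LUCAS algorithm, since its first step is manual. This classifies patients for analysis only and changes nothing in care.
- Reconcile the crossover clause with the requirement to have completed the study treatment. Keeping crossovers in their randomised arm is preferable to dropping them, because dropping also selects on outcome: excluding the 5% with 80% survival in the example would leave 28.4% against 25%, or 3.4 points instead of 6.
- Label any analysis by treatment received as exploratory. If an effect of receiving the device is wanted, a complier-average (instrumental-variable) estimate is one option.

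The cost is a change of wording and slight extra analysis work. Analysing by randomised arm needs only the allocation, so no new data are required.
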